### Methods of analysis

#### Clinical outcomes

##### Primary objective

Primary outcome

PAC-QOL scores at the time-points T0, T12, T24, T36 and T48 weeks in the three arms will be analysed using a mixed linear regression model, with random effects for participants and a fixed effect of time since randomisation (potentially considering a random effect for time as well to relax the assumption of same time trend for each participant) to estimate mean differences between PAC-QOL score before and after LVMR. The comparison of primary interest is between the score at 24 weeks after surgery and the score at baseline. Missing data will be imputed through multiple imputation by chained equations.

Secondary outcome

PAC-SYM scores will be analysed by the same approach as described above.

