#### Randomisation procedures

Randomisation will be delivered following recruitment (after full eligibility and all baseline assessments). Randomisation will be stratified by sex and female participants further stratified by centre. The Pragmatic Clinical Trials Unit (PCTU) has developed a validated online randomisation system, which will be accessed by suitably trained and delegated researchers at recruiting sites and will follow the PCTU approved standard operating procedure (SOP) for the study.

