##### Other baseline-only assessments

Other baseline-only assessments comprise:Constipation (2006) and IBS (2006) modules of the Rome III questionnaireCleveland Clinic constipation questionnaire [97]Brief, chronic pain, autonomic and joint hypermobility assessments

Randomisation will be performed only once full eligibility has been confirmed and all baseline assessments taken (which may require INVEST). Urinary pregnancy testing will be made available to women of child-bearing potential at eligibility assessment and advice will be given to all women on the need to prevent pregnancy during the study intervention period.

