#### Visit 2 - run-in for surgical interventions

Participants will be randomized (at visit 1) to three arms with different lengths of delay before surgery. In all arms there will be a period of 4 weeks post-eligibility to arrange the logistics of surgery (T–4w to T0) and ensure that patients have returned to their normal life routine after various assessments. Subsequently, LVMR will be performed at T0 in group I (visit 2); T12 (12 weeks) in group II (visit 3) and T24 (24 weeks) in group III (visit 4).

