#### Visit 2–8 - follow-up outcome assessments

All patients will complete the standardised outcome framework (inclusive of PAC-QOL and PAC-SYM) questionnaires at T–4, T0 and 12, 24, 36, 48, 60 and 72 weeks post run-in (see Additional file 2). This ensures that 24-week and 48-week post-surgery follow-up data on the primary and secondary outcomes are collected in all patients, whilst maintaining blinding of group allocation. Thereafter, participants will leave the study and return to “routine clinical care” as determined within their local NHS institution. During the first 24 weeks post-surgery patients will be quarantined from further intervention, excepting emergency interventions (e.g. for complications).

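### The primary model omits T-4, the only PAC-QOL score taken before randomisation, and does not say which visit is baseline

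*Protocol article*

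**What the plan says.** The protocol article, Methods of analysis, Primary objective, gives the visits that enter the primary model: "PAC-QOL scores at the time-points T0, T12, T24, T36 and T48 weeks in the three arms will be analysed". The model is a mixed linear regression "with random effects for participants and a fixed effect of time since randomisation", possibly with a random time effect as well. No other covariate is named. The contrast is then fixed: "The comparison of primary interest is between the score at 24 weeks after surgery and the score at baseline".

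The section on Visits 2–8 gives the collection schedule: "questionnaires at T–4, T0 and 12, 24, 36, 48, 60 and 72 weeks post run-in". So T-4 is collected and T0 is a separate, later assessment.

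On timing, the section on other baseline-only assessments says: "Randomisation will be performed only once full eligibility has been confirmed and all baseline assessments taken". The Visit 2 section adds "Participants will be randomized (at visit 1) to three arms with different lengths of delay before surgery" and "In all arms there will be a period of 4 weeks post-eligibility to arrange the logistics of surgery", and labels that period as T-4 to T0. The Blinding section says that patients know their allocated waiting time.

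On stratification, Randomisation procedures says: "Randomisation will be stratified by sex and female participants further stratified by centre". The models for the secondary objectives adjust for baseline values, gender and breakthrough medication, but centre is not named.

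**The concern.** Two things in the primary analysis text do not fit together.

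First, the list of visits leaves out the one PAC-QOL score that randomisation guarantees to be comparable across arms. T0 comes after randomisation. By then a participant in group I expects surgery at once and one in group III expects to wait 24 weeks, and PAC-QOL is self-reported.

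Second, the contrast refers to baseline without naming the visit. Elsewhere in the protocol, baseline is the visit 1 assessment. If that is meant here too, the reference score is not among the listed data. If T0 is meant, the reference is an open-label score taken after randomisation.

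At stake are some precision from data that are already collected, and a route by which knowledge of the allocation could enter the estimate through T0.

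**Working it through.** **Inputs.** From Sample size: SD 1.5, correlation 0.5 between repeated assessments (0.3 and 0.1 also considered), difference 1.0 point, 5% significance (two-sided assumed), 34 per arm, 10% loss. From Design/methods: surgery at T0, T12 and T24 in groups I, II and III. From Primary objective: visits T0, 12, 24, 36 and 48. Assumed: T0 is answered before surgery in group I, and T-4 is the visit 1 score.

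**Model.** Categorical time, with separate effects at 12, 24, 36 and 48 weeks after surgery. There is no arm term, so pre-surgery means are common to all arms at each visit. With X_g the design matrix of arm g and V the covariance of one participant's scores:

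- Var(estimates) = [Σ_g n X_g′ V⁻¹ X_g]⁻¹; SE is the root of the entry for the 24-week effect.
- Power = Φ(1.0/SE − 1.96).

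**Step 1: the plan's own figure.** Visits T0–T48, r = 0.5, n = 34: SE = 0.2759. Power = Φ(3.62 − 1.96) = 95.2%. The smallest n for 95% power is 34. 34/0.9 = 37.8, so 38 per arm and 114 in total. This is the protocol's figure, reached without T-4. At 38 per arm, power is 94.5% at r = 0.3 and 94.6% at r = 0.1, consistent with the stated minimum of 90%.

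**Step 2: add T-4 (34 per arm).**

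| Correlation | SE, T0–T48 | SE, with T-4 | Variance reduction | Power | n per arm for 95% |
|---|---|---|---|---|---|
| 0.5 exchangeable | 0.2759 | 0.2556 | 14% | 95.2% → 97.5% | 34 → 29 |
| 0.3 exchangeable | 0.2972 | 0.2856 | 7.6% | 92.0% → 93.8% | 40 → 37 |
| 0.1 exchangeable | 0.2961 | 0.2940 | 1.4% | 92.2% → 92.5% | 39 → 39 |
| AR(1), 0.5 per 12 weeks | 0.317 | 0.317 | 0% | 88.4% → 88.4% | not computed |

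For the first row, 0.2556²/0.2759² = 0.0653/0.0761 = 0.86.

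**Step 3: influence of T0.** The 24-week estimate is a weighted sum of arm-by-visit means. At r = 0.5 with T0–T48, T0 has weight −0.50 in group I and +0.47 in group III. Suppose, purely for illustration, that knowing the allocation opens a 0.3-point gap at T0, half in each of these groups:

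- T0–T48: 0.15 × (0.50 + 0.47) ≈ 0.15.
- With T-4 added, the weights become −0.346 and +0.325: 0.15 × (0.346 + 0.325) ≈ 0.10.
- With T-4 in place of T0: no contribution from T0. SE = 0.276, as in Step 1, because under exchangeable correlation either pre-surgery score carries the same information.

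At r = 0.3 the first two figures are 0.091 and 0.071. Under AR(1), adding T-4 does not change the T0 weights. The direction depends on the shift: if group I feels better at T0 because surgery is imminent, the bias is towards no effect; if it feels worse, away from it.

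**Step 4: sex and centre.** The protocol gives no figure for what these explain. If they account for 2%, 5% or 10% of total variance (assumed), the variance of the 24-week effect at r = 0.5 falls by 0.8%, 2.2% or 4.6%.

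**The case against.** The best defence is that nothing stated is wrong. The 34 per arm and 95% power reproduce from T0–T48 alone, T0 precedes surgery in every arm, and the study rationale states the design assumption that no treatment effect is expected before surgery. The article is condensed, the covariate list may sit in the analysis plan, and the reference to baseline may already mean T-4. The participant random effect absorbs much of any difference by sex or centre.

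Much of this stands. A reader might infer that the trial is underpowered without T-4, or that the plan deliberately discards it; the documents support neither. A reader might also infer that the estimate is biased because T0 follows randomisation. The protocol gives no evidence of a shift at T0, and the 0.3-point gap is an assumption without a source. Nor would adding T-4 cure such a bias while T0 stays in the model: about 70% of it remains (0.10 of 0.145). An effect of waiting on the open-label scores at T12 and T24 would not be touched either.

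What does not fall away is the text itself. The article does not leave the visits to a later document. It lists them, omits T-4, and then refers to a baseline that the list does not identify. The design assumption concerns the effect of surgery; it does not rule out a change in self-reported quality of life on learning the waiting time.

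**Conclusion.** The concern holds as an ambiguity to resolve and an inexpensive improvement, not as an error in power or a demonstrated bias. The primary model's visit list excludes the only PAC-QOL score taken before randomisation, and the baseline in the primary contrast is not tied to a visit.

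Using T-4 lowers the variance of the 24-week effect by 14%, 8% or 1% at exchangeable correlation 0.5, 0.3 or 0.1, and not at all under AR(1) decay. The upper figure rests on the protocol's single correlation of 0.5 applying to every pair of visits. The precision gain and full removal of T0-driven bias cannot be had together: keeping both visits gives the gain and leaves part of any bias; replacing T0 with T-4 removes that part and returns the SE to 0.276.

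The stratification factors are a secondary matter, probably small, with no size computable from the document. That participants know their allocation by T0 is inferred from randomisation at visit 1 and the four-week interval; the protocol does not state the day on which they are told.

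**What to change.** - Define baseline in the primary analysis as the pre-randomisation T-4 score, and use the term in that sense throughout.
- Add T-4 to the visits in the primary mixed model, with a mean common to all arms.
- Include the stratification factors, sex and centre (centre as fixed or random).
- Report the mean T-4 to T0 change by arm, as a check for an effect of knowing the allocation.
- Specify a sensitivity analysis with T-4 in place of T0. It removes any T0-driven part at the same SE (0.276) under exchangeable correlation, but gives up the precision gain.

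The cost is wording in the analysis plan, one more row per participant from data already collected, a few degrees of freedom for centre, and one extra model run. The sample size need not change. The wording should be settled before the analysis plan is signed off.

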## Design/methods

This is a stepped-wedge, randomised trial of LVMR in adults with chronic constipation (*n* = 114), which follows the “Standard Protocol Items: Recommendations for Interventional Trials” (SPIRIT) guidelines (see Additional file 3). Participants will be randomized to three equal arms (*n* = 38) with different lengths of delay before surgery. LVMR will be performed at T0 in group I; T12 (12 weeks) in group II and at T24 (24 weeks) in group III.

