### Statistical considerations

#### Sample size

The sample size has been calculated using the primary clinical outcome, a change in mean PAC-QOL score [74]. This widely used, psychometrically robust measure of overall treatment response with concurrent validity for patient global ratings of success has been used in previous trials of behavioural therapies and surgical trials [52] (including trials of LVMR) in CC [75]. For a chronic condition such as CC, a difference of 1.0 point in the primary outcome (score range = 1–4) can be considered clinically important and also the notional minimum required to justify the cost and invasive nature of LVMR, or of a more complex and expensive treatment.

Previous trials have shown a 1-point decrease in PAC-QOL from pre-operative to 48 weeks (1 year) post-surgery [52]. Using a stepped-wedge design, we hypothesize that PAC-QOL score at any time point during follow up will be approximately 1.0 point lower than in participants pre-operatively.

Sample size was calculated by simulation using the simsam package in Stata [98]. We assumed PAC-QOL follows a normal distribution over all time points with a standard deviation of 1.5 and with correlation between repeated assessments equal to 0.5.

Simulation shows that detection of a 1.0-point difference in 6-month PAC-QOL, with 95% power (purposely chosen to reflect the magnitude and risk of the intervention) at the 5% significance level, requires 34 participants in each of the three arms. Allowing for a 10% loss to follow up, a sample size of 38 is needed per arm (i.e. a total sample size of 114 patients across the three arms). Should the correlation between repeated assessments be lower than 0.5, a sample size of 114 will still provide at least 90% power for the study. This was calculated using the same simulation procedure with correlations of 0.3 and 0.1.

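### If correlation between visits decays over time, the random-participant-effect model makes the standard error of the 24-week contrast about 3-7% too small (type I error roughly 6-7% instead of 5%)

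*Protocol article*

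**What the plan says.** Under Methods of analysis, Primary objective, the data are "PAC-QOL scores at the time-points T0, T12, T24, T36 and T48 weeks in the three arms". The model is a "mixed linear regression model, with random effects for participants and a fixed effect of time since randomisation". One relaxation is left open: "potentially considering a random effect for time as well to relax the assumption of same time trend for each participant". The target is then named: "The comparison of primary interest is between the score at 24 weeks after surgery and the score at baseline". PAC-SYM is to be analysed in the same way.

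Under Sample size, the simulation assumes a "standard deviation of 1.5 and with correlation between repeated assessments equal to 0.5". The sensitivity check repeats it with correlations of 0.3 and 0.1. Each of these is again a single value for all pairs of visits.

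The article names no robust variance, no serial correlation and no participant-specific effect of surgery.

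**The concern.** A participant random intercept implies that two scores 12 weeks apart are as strongly correlated as two scores 48 weeks apart, and that every patient shifts by the same amount after surgery. Over a year of a symptom-driven score, the first may fail. The protocol itself gives reason to doubt the second: the Background says surgery can leave some patients functionally worse, and pre-operative determinants of outcome are a secondary objective.

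In this design the 24-week effect is assembled from within-person contrasts over different lags, so its model-based standard error depends on the assumed covariance. If the correlation decays, the primary interval is somewhat too narrow and the p-value somewhat too small. The direction favours declaring benefit in a trial that is meant to decide whether a mesh operation works.

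**Working it through.** **Inputs from the protocol.** Three equal arms with surgery timed as "LVMR will be performed at T0 in group I; T12 (12 weeks) in group II and at T24 (24 weeks) in group III"; five assessments; SD 1.5; correlation 0.5; target difference 1.0; 5% level; 34 evaluable per arm.

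**Assumptions added.** The test is two-sided. The assessment at the time of surgery is pre-operative. Time is categorical, and separate effects are fitted at 12, 24, 36 and 48 weeks after surgery.

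**Formulas.** Let X_g be the design matrix of arm g, R the fitted common-correlation matrix, s² the fitted variance, V the true covariance and A = Σ n X_g′R⁻¹X_g.
- Reported variance: s²A⁻¹, with R and s² at the values the fit converges to under V.
- True variance: A⁻¹(Σ n X_g′R⁻¹VR⁻¹X_g)A⁻¹.
- Type I error = 2Φ(−1.96 × reported SE / true SE).
- Power = Φ(1.0/SE − 1.96).

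**Step 1: the plan's own figure.** With correlation 0.5 and 34 per arm, SE = 0.276 and power = Φ(3.62 − 1.96) = 95.2%. With 33 per arm, SE = 0.276 × √(34/33) = 0.280 and power is 94.6%, so 34 is the smallest number that works. At correlations 0.3 and 0.1 and 34 per arm, SE is 0.297 and 0.296 and power is 92.0% and 92.2%. The stated sample size and the 90% floor are reproduced, so this is very likely the intended model. A single constant effect would need only 15 per arm. Under common correlation the reported and true SE coincide and the type I error is 5.0%.

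**Step 2: decaying correlation, SD held at 1.5, 34 per arm.**

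| True correlation | Reported SE | True SE | Too small by | Type I error |
|---|---|---|---|---|
| Linear, 0.6 (12 weeks) to 0.4 (48 weeks) | 0.270 | 0.276 | 2.2% | 5.5% |
| Linear, 0.6 to 0.3 | 0.276 | 0.285 | 3.1% | 5.8% |
| 0.4 + 0.6 × 0.3^lag | 0.277 | 0.292 | 5.1% | 6.3% |
| 0.4 + 0.6 × 0.5^lag | 0.260 | 0.278 | 6.6% | 6.7% |
| AR(1), 0.7 | 0.272 | 0.294 | 7.4% | 7.0% |
| AR(1), 0.5 | 0.297 | 0.321 | 7.4% | 7.0% |

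Under AR(1) 0.7, power is Φ(1/0.294 − 1.96) = 92.5%.

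**Step 3: variable response to surgery.** Take response SDs of 0.5, 0.75, 1.0 and 1.25 and let response correlate negatively with the pre-operative level, so that the post-operative SD stays at 1.5. Type I error is then 5.2%, 5.4%, 5.7% and 6.0% under common correlation 0.5. With AR(1) 0.7 it is about 7.1% to 7.7%. If the response variance is added on top, type I error is 6.2%, 6.9% and 7.8% for SDs of 0.75, 1.0 and 1.25. The post-operative SD then becomes √(2.25 + 0.5625) = 1.68, √(2.25 + 1) = 1.80 and √(2.25 + 1.5625) = 1.95.

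**Step 4: the optional random time effect.** Across the scenarios examined, which include added response variance, an independent random slope leaves the SE 4-9% too small (0.7-2% in the mild cases). A correlated slope leaves it up to 13.5% too small. A trend over calendar time is not a step at surgery.

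**Step 5: simulated rejection rates under the null** (3,000 trials, 38 per arm, Monte Carlo error about 0.4 points).

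| True covariance | Model-based | Participant-clustered |
|---|---|---|
| Common 0.5 | 5.5% | 5.8% |
| AR(1), 0.7 | 6.9% | 5.6% |
| 0.3 + 0.7 × 0.5^lag | 7.6% | 5.7% |

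Unstructured covariance gave 5.4-6.7% over all scenarios simulated. These runs used normal critical values, without small-sample degrees of freedom.

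**The case against.** The strongest reply is that this is detail for the analysis plan. The Blinding section promises such a plan, signed off before any quantitative analysis, and the article names no method for the standard error. That is partly right: an unseen plan may specify a robust variance. But the article does state the model that determines the standard error, offers one specific relaxation that does not address the problem, and tests only common correlations in the sample size. It can be judged on those choices.

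The second reply is that the article supplies neither a rate of decay nor a response variance. This stands. Mild decay gives about 5.5%, and pure AR(1) is a strong choice: at a lag-one value of 0.5 to 0.7 the T0-T48 correlation is only 0.5⁴ = 0.06 to 0.7⁴ = 0.24.

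Third, a reader might infer a shortfall of up to 12% and a type I error near 9%. The document does not support that. Those values need response variance that pushes the post-operative SD above the stated 1.5, combined with decay, or else a correlated random slope. On the stated 1-4 score range no SD can exceed (4 − 1)/2 = 1.5. Response variation with zero mean effect also describes a null in which benefit and harm cancel, not one in which surgery does nothing.

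Fourth, the consequence is limited. Power of 92.5% under AR(1) 0.7 still exceeds the 90% the protocol accepts for lower correlations. A true 1.0-point effect would lie 1/0.294 = 3.4 standard errors from zero.

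**Conclusion.** The point holds at moderate size. Under the protocol's own common correlation the standard error is correct. If correlation decays with the interval between visits, the model-based SE of the 24-week contrast is about 3-7% too small and the type I error is roughly 6-7%. Variable response adds little while the post-operative SD stays at 1.5, and more only if the SD rises above it.

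This rests on an assumed decay and on effects specific to time since surgery, which fits the stated 24-week comparison and reproduces the 34 per arm. With one constant surgery effect, the plain random intercept is close to nominal in most scenarios (reported-to-true SE ratio 0.97-1.07), although adding the random slope there makes the SE about 2-14% too small. It would be wrong to say that the primary interval is certainly too narrow. What can be said is that its validity depends on an assumption the plan has not varied, and that protection is cheap.

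**What to change.** Keep the mixed model. State that the primary standard error, confidence interval and p-value come from a participant-clustered (sandwich) variance with a small-sample correction. Alternatively, specify an unstructured within-participant covariance over the five visits. Let this fixed choice replace the phrase "potentially considering a random effect for time as well", and apply it to PAC-SYM as well.

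The cost is a sentence of analysis text and an option in standard software. Intervals become slightly wider when the common-correlation model does not hold, and little is lost when it does. The change removes most of the inflation, but a small excess over 5% may remain at this sample size.

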### Specific study rationale

The overall rationale is to address the main objectives (see below) within a controlled trial. We have used a stepped-wedge, randomised trial design which permits observer-masked data comparisons between patients awaiting intervention with those who have undergone surgery. Contrary to most stepped-wedge trials individual patients are randomised rather than clustered. In brief (more detail below), eligible participants based on clinical evaluation and radio-physiological investigations (INVEST) will be randomised to three arms with different lengths of delay before surgery (see Additional file 2). In all arms there will be a period of 4 weeks post-eligibility to arrange the logistics of surgery (time (T)–4 weeks to T0) and ensure that patients have returned to their normal life routine after various assessments. LVMR will be performed at T0 in group I; T12 (12 weeks) in group II and T24 (24 weeks) in group III. Unavoidably, participants will be aware when surgery is undertaken: this, however, fortuitously meets the assumptions of the stepped-wedge design, i.e. no effect of treatment is expected until surgery has been performed. Efficacy outcome data will be collected at equally stepped time points (T0, 12, 24, 36 and 48 weeks).

This is, in effect, a modification of a standard, parallel-arm, wait-list control design, but with several advantages. First, a stepped-wedge design is more efficient and thus improves recruitment feasibility (the bane of nearly all surgical trials). Despite the multicentre approach of this study, the problems of recruitment cannot be underestimated. Simulation demonstrates that a parallel-arm design requires a much larger sample size than that proposed for the current study at the same power. Secondly, the trial design means that there is only a one in three chance (rather than one in two for a parallel arm) of waiting 6 months for surgery, which is more acceptable to patients.

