### Trial objectives and endpoints

#### Primary objective

The primary objective is to determine the clinical efficacy of LVMR compared to controls at short-term follow up (24 weeks).

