### Trial outcomes

#### Primary outcome

The primary clinical efficacy endpoint is based on the Patient Assessment of Constipation-Quality of Life (PAC-QOL) questionnaire total score (analysed as a continuous variable) in patients at 24 weeks post-surgery compared to pre-surgery controls. The secondary clinical efficacy endpoints are based on the Patient Assessment of Constipation Symptoms (PAC-SYM) questionnaire total score (analysed as a continuous variable) in patients at 24 weeks post-surgery compared to pre-surgery controls.

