#### Secondary outcomes

All outcomes within the standardised outcome framework will be analysed to compare baseline values with values at 24 and 48 weeks post-surgery follow up. When further follow-up data are obtained (time permitting) these will also be reported at the later time points of 60 and 72 weeks. The outcomes are:Response to treatment defined as a 1-point (or greater) reduction in the PAC-QOL score [74, 75].PAC-QOL: individual domains and total score (as continuous variables).PAC-SYM score: individual domains and total score (as continuous variables).A 2-week patient diary (for 2 weeks prior to each assessment) to record bowel frequency and whether each evacuation was “spontaneous (no use of laxatives) and/or complete”; a journal will also capture concurrent medication, health contacts, time away from normal activities (including work) since the patient’s last visit.Generic QOL assessment: EuroQol Health Outcome measure (EQ-5D)-5L descriptive system and EQ-visual analogue scale (VAS) [76]. Note: the EQ-VAS has SD of approximately 30 points: a 10% difference in VAS deemed clinically significant can be detected with the large sample sizes proposed.Patient Health Questionnaire-9 (PHQ-9) [58, 59].Generalized anxiety disorder questionnaire (GAD7) [60].Global patient satisfaction/improvement score (VAS) and whether they would recommend LVMR to other patients.Potentially modifiable cognitive and behavioural psychological variables shown to predict onset and perpetuation of other functional bowel symptoms: negative perfectionism [71], avoidant and “‘all or nothing” behaviour subscales of the behavioural response to illness questionnaire (CC-BRQ) [77], and brief illness perception questionnaire (BIPQ) (CC) [78].St Marks Incontinence score (for concurrent symptoms) [79].Baseline brief sexual function questionnaire (Pelvic Organ Prolapse/Urinary Incontinence Sexual Questionnaire (PISQ-12) in women [80] and Male Sexual Health Questionnaire (MSHQ)-EjD Short Form in men [81]).

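### The analysis section names 24 weeks after surgery versus baseline as the primary comparison, contradicting the controlled endpoint, and it does not define baseline

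*Protocol article*

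**What the plan says.** The Protocol article describes the primary comparison in several places, and they do not agree.

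- Primary objective, under Trial objectives and endpoints: "to determine the clinical efficacy of LVMR compared to controls at short-term follow up (24 weeks").
- Primary outcome, under Trial outcomes: PAC-QOL total score "in patients at 24 weeks post-surgery compared to pre-surgery controls".
- Specific study rationale: the design "permits observer-masked data comparisons between patients awaiting intervention with those who have undergone surgery".
- Methods of analysis, Primary objective: PAC-QOL at T0, T12, T24, T36 and T48 in all three arms goes into a mixed linear model "with random effects for participants and a fixed effect of time since randomisation", fitted "to estimate mean differences between PAC-QOL score before and after LVMR". The next sentence is: "The comparison of primary interest is between the score at 24 weeks after surgery and the score at baseline".

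The analysis section says PAC-SYM follows the same approach. Under Secondary outcomes, the standardised outcome framework "will be analysed to compare baseline values with values at 24 and 48 weeks post-surgery follow up". The analysis text for the secondary objectives adjusts for baseline values, gender and breakthrough medication; time since randomisation is not on that list.

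Scores are collected at both T-4 and T0, and groups II and III have later scores before their operations. The word baseline in the primary analysis could mean any of these.

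**The concern.** A score 24 weeks after surgery minus a baseline score equals the surgical effect plus whatever would have happened without surgery over the same interval. The objective, the endpoint and the design rationale all ask for the first part alone. The sentence that fixes the primary contrast asks for the sum.

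The second part may well not be zero. Participants enter after conservative treatment has failed and while reporting problematic symptoms, so regression to the mean, natural course and trial attention could all move PAC-QOL downwards. The Background names reliance on observational case series as the evidence gap. An uncontrolled change reported as the primary result would repeat that weakness within a randomised trial.

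The model paragraph does not settle which quantity is reported. It names a time term but no explicit surgery term, so an analyst following the sentence to the letter could report the before/after change.

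**Working it through.** **Inputs from Sample size and Design/methods.** Difference 1.0; SD 1.5; correlation between repeated assessments 0.5; significance level 5% (taken as two-sided; the article does not say); power 95%; 34 evaluable per arm, 38 after 10% loss, 114 in total; surgery at T0, T12 and T24; model time points T0 to T48.

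**1. Reproducing the plan's sample size.** I took the generalised least squares variance of the stepped-wedge model with time as visit categories, separate effects for 12, 24, 36 and 48 weeks since surgery, exchangeable correlation, and a score on the day of surgery counted as pre-surgery (an assumption).

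- SE of the 24-week effect with 34 per arm: 0.276.
- Power = Φ(1.0/0.276 − 1.96) = 95.2%. With 33 per arm it is 94.6%, so 34 is the smallest number that reaches 95%. A simulation of 5,000 trials gave 94.4%.
- Inflation: 34/0.90 = 37.8, so 38 per arm and 114 in total.
- At correlations 0.3 and 0.1, 38 per arm gives 94.5% and 94.6%, in line with the stated minimum of 90%.

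Other readings compare as follows:

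| Contrast | Per arm for 95% power |
|---|---|
| Time-adjusted 24-week effect, categorical time | 34 |
| Same, linear time | 32 |
| One constant effect, categorical time | 15 |
| Before/after change pooled over arms | about 10 |

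The pooled figure is (1.96 + 1.645)² × 1.5² × 2(1 − 0.5)/1.0² = 29.2, so 30 in total. A paired test within a single arm needs 32, but at correlation 0.1 its power is only 0.80 (n = 34) to 0.85 (n = 38), below the stated 90%.

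**2. The sentence read literally.** Pooled over 3 × 34 = 102 patients:

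SE = 1.5 × √(2 × (1 − 0.5)/102) = 0.149.

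With no surgical effect and a total untreated improvement d, the chance of a significant result is Φ(d/0.149 − 1.96) + Φ(−d/0.149 − 1.96). The documents give no value for d, so these are assumptions:

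| Assumed d (points) | Declared significant |
|---|---|
| 0.1 | 10% |
| 0.2 | 27% |
| 0.3 | 52% |

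**3. Drift stated per 12 weeks.** If baseline is T0, the interval to 24 weeks after surgery is 24 weeks in group I, 36 in group II and 48 in group III: 2, 3 and 4 steps, 3 on average. Assumed improvements of 0.05, 0.10 and 0.20 points per step therefore give a false effect of 0.15, 0.30 and 0.60 points. In simulation (5,000 trials each, 34 per arm, no surgical effect):

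| Drift per 12 weeks | Literal contrast significant | Time-adjusted effect significant |
|---|---|---|
| 0.05 | 17% | 5.4% |
| 0.10 | 53% | 5.2% |
| 0.20 | 98% | 5.0% |

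The mean time-adjusted estimate was 0.00 to two decimals in every case.

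**4. How much of the control is concurrent.** Group II reaches 24 weeks after surgery at T36 and group III at T48. By then everyone is scheduled to have been operated. Only group I versus group III at T24 sets a 24-week effect against patients still waiting at the same time. That comparison alone, 34 per arm, has SE 1.5 × √(2/34) = 0.364 and power 78.5%. Adjusted for baseline, the SE is 0.364 × √(1 − 0.5²) = 0.315 and power 88.8%. The 95.2% depends on what the model borrows from the other arms and times.

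**The case against.** The strongest reply is that one loosely worded sentence is being read without the one before it. That sentence specifies a model over three arms with a fixed effect of time since randomisation. Because surgery dates are randomised, the time term is estimated partly from participants still waiting, so the model's surgery effect is net of untreated change. In a stepped-wedge design the control data are the pre-surgery observations, so the endpoint and the analysis sentence may be two wordings of one contrast. The sample size supports this: it matches the time-adjusted effect and not the pooled before/after change.

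Much of this stands. A reader might infer that the plan throws away the randomised control and fixes each patient's own change as the primary result. The article does not support that: it says the score at baseline, not the patient's own, and the model can deliver the controlled effect. The false-positive rates above belong to the literal reading under assumed drifts, not to the model.

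What does not stand is that the model alone resolves the matter. Within a model holding both time and surgery terms, the fitted score 24 weeks after surgery minus the fitted score at baseline still includes the time change. Only the surgery effect removes it, and that is not what the sentence names.

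Two limits apply. A controlled contrast does not cure expectation effects in a self-reported outcome, because patients know whether they have been operated. And a separate analysis plan, which the Blinding section requires before any quantitative analysis, may already settle the wording; it is not shown, and the published sentence contradicts the published endpoint either way.

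**Conclusion.** The point holds as a contradiction in the stated primary contrast, together with an undefined baseline. Followed literally, the sentence gives a wrong answer whenever untreated scores change: the bias equals the untreated change point for point, and the smaller standard error (0.149 against 0.276) makes modest drifts look significant. Assumed total improvements of 0.1 to 0.3 points give about 10% to 52% false positives. The time-adjusted effect is unbiased provided the time trend is common to the three arms.

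These figures rest on the plan's SD and correlation, exchangeable correlation, a two-sided 5% test and assumed drift sizes. The match with 34 per arm suggests that the controlled effect is what the trial was sized for, so the text should be brought into line with the design and not the reverse.

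**What to change.** Replace the sentence with: *The primary estimate is the model's effect of LVMR at 24 weeks since surgery relative to not-yet-operated participants, adjusted for time since randomisation as visit categories, with separate effects by time since surgery.*

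- Use the same effect for PAC-SYM and for the 24-week secondary outcomes, and add time since randomisation to the secondary models.
- Define baseline once (T-4, T0 or last pre-operative score) and report change from it as descriptive.
- State that results at 48 weeks after surgery and later have no concurrent untreated comparison.
- State that only group I versus group III at T24 is fully concurrent for the 24-week effect, the rest being borrowed through the model.

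The cost is wording in the protocol and analysis plan. The sample size stays at 34 evaluable and 38 randomised per arm, 114 in total. The confidence interval will be wider than for the before/after contrast, by the ratio 0.276/0.149, about 1.9.
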